### Statistical analysis

At the outset, the psychometric quality of the concepts measured in the questionnaires will be tested by exploratory and confirmatory factor analysis as well as an exploratory structural equation modelling. These analyses will enable the confirmation of the internal validity of the concepts postulated in the measurement scales and will, if needed, enable the adjustment or rejection of invalid in our sample. The analyses will be conducted under Mplus8 for Windows.

At the individual level, mixed linear models will used to assess the effects of the intervention on each outcome, while taking into account the hierarchical nature of the data, and possible variations in the implementation of the intervention protocol from one department or unit to another. The score of an outcome at T2 is thus explained by the fixed SC effect (intervention versus control) and by the random effect of the department or unit. A statistical adjustment will be made on the outcome score at T0 and on age, gender, profession, working time and size of the team, in line with the literature [36, 80]. The ICC will be estimated to have a precise idea of the effect of the department or unit.

Given the results obtained by Dahinten (2014), which showed a moderating effect of the level of implication at T0 on the impact of the intervention on implication at T1, a second model will be run each time including an interaction terms between the SC group and baseline measures of the outcome variable. These analyses should enable the identification of conditions that favour or undermine the interventions’ effect and implementation.

For the psychometric scales more particularly, the analyses will be performed on both the overall scores and the sub-dimension scores so as to refine the analysis of the effects as far as possible.

At the department and unit level, the score for each outcome will be calculated at T0 and T2 in each group. Mixed-effects linear models will be used to test the effects of the intervention over time, and between departments or units. These analyses will enable the study of variations in the effects of the intervention across the “intervention SC” departments or units.

The alpha risk retained for the statistical analysis is 5%. If the proportion of missing data exceeds 30%, multiple imputation will be considered.

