## Methods/design

### Study design

This study is a randomised controlled trial conducted in a large university hospital centre in France.

The psycho-social intervention lasts 12 months. It simultaneously targets healthcare teams, department management and SC management. The randomisation was therefore performed at SC level.

The quantitative study of the effects of the intervention combines an assessment via self-administered questionnaire and the collection of clinical indicators in the course of a mandatory medical check-up in the occupational medicine department in the CHU. Three assessment times are planned: a baseline assessment, an assessment immediately after the intervention and an assessment 1 year after the end of the intervention (Fig. 1).

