### Objectives

To assess the impact at one and 2 years of a standardised psychosocial intervention programme on the structural empowerment score in an “intervention SC”, in comparison with a “control SC”.To assess the impact of the intervention at one and 2 years on psychological empowerment scores.To detail the effects of the intervention on sub-dimensions of structural and psychological empowerment.To assess the effect of the intervention on motivational processes and factors.To assess the effect of the intervention on managerial practices.To assess the impact of the intervention on working conditions, health and performance.

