The collection of indicators at 1 year and 2 years is performed in the same manner.

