
### The control SC

The “control SC” is merely subject to the annual occupational medicine follow-up, providing the measures at T0, T1 and T2. The participants in the quantitative study carried out at the time of the check-ups are in no way informed of the randomisation to come or the future accompaniment of one of the two SCs. This system makes it possible to dissociate the mandatory health follow-up by occupational medicine from the quantitative study that is common to the two SCs on the one hand, and the collective intervention specific to the “intervention SC” on the other. Thus all participants undertake to be followed up in the long term independently from any intervention.

During the intervention period in the “intervention SC”, the “control SC” functions in the normal manner for the CHU, according to the usual decision-making provisions.

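### The objectives cover one and two years, but both written analyses use only T0 and T2, so the one-year effect has no stated model

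*Protocol article*

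**What the plan says.** The first two objectives name two time points. For structural empowerment: "To assess the impact at one and 2 years of a standardised psychosocial intervention programme on the structural empowerment score". For psychological empowerment: "To assess the impact of the intervention at one and 2 years on psychological empowerment scores". The remaining objectives name none.

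The Study design section plans three assessments: "a baseline assessment, an assessment immediately after the intervention and an assessment 1 year after the end of the intervention". The section on the control SC labels them, "providing the measures at T0, T1 and T2", and the data collection section confirms both follow-up waves: "The collection of indicators at 1 year and 2 years is performed in the same manner". The intervention lasts 12 months, so T1 is the one-year, end-of-programme visit and T2 the two-year visit.

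The Statistical analysis section then defines two analyses. At individual level, "The score of an outcome at T2 is thus explained by the fixed SC effect" and by a random department or unit effect, adjusted for the T0 score and for age, gender, profession, working time and team size. At department or unit level, "the score for each outcome will be calculated at T0 and T2 in each group". The only T1 in that section belongs to a result of a cited earlier study, given as the reason for an interaction model.

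**The concern.** The objectives and the analysis rules do not match. A statistician who follows the analysis section to the letter produces a two-year contrast and nothing at one year, so half of each of the first two objectives goes unanswered.

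The missing half matters. T1 comes directly after the programme ends and T2 a year later. A null result at T2 alone cannot separate a programme that never worked from one that worked and then faded. A positive result at T2 alone cannot show whether the gain came early or late.

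Two further consequences follow. With no stated one-year model and no primary time point, both could be settled after the data are seen. Also, the Sample size section itself expects substantial loss to follow-up, yet someone seen at T0 and T1 who misses T2 drops out of the individual-level model altogether.

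**Working it through.** **1. Time points, section by section**

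| Section | One year (T1) | Two years (T2) |
|---|---|---|
| Objectives 1 and 2 | yes | yes |
| Study design; Data collection; The control SC | collected | collected |
| Statistical analysis, individual level | no model | response, adjusted for T0 |
| Statistical analysis, department/unit level | not included | included, with T0 |
| Discussion | analysis to be reported | analysis to be reported |

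T2 cannot be read as the one-year visit, because three labels are attached to three visits. If it could, the two-year objective would lack a model instead. The department/unit paragraph does speak of effects over time, but the scores it analyses are those at T0 and T2.

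**2. Does the sample size settle the time point?**

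Inputs from the Sample size section: difference 0.12, SD 0.56, alpha 5% (two-sided assumed), power 80%, ICC 0.001.

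- Before inflation: n0 = 2 × [0.56 × (1.960 + 0.842) / 0.12]² = 341.9, or 342 per group.
- Inflation with the whole SC as one cluster: n = n0 × [1 + (n − 1) × 0.001], so n = 341.9 × 0.999 / (1 − 0.3419) = 519. The stated figure is reproduced (design effect 519 / 342 = 1.518).

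This is the size for one comparison of one difference. The section describes that difference as a change within the intervention group between T1 and T2, which is neither the T1 nor the T2 contrast between SCs. It therefore does not show which time point is primary.

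For illustration, suppose T1 and T2 were tested as co-equal at 5% each. The family-wise error would be 1 − 0.95² = 9.75% if the tests were independent. With Bonferroni at 2.5% each, n0 becomes 2 × [0.56 × (2.241 + 0.842) / 0.12]² = 414, and 414 × 0.999 / (1 − 0.414) gives about 706 per group after inflation. The planned recruitment is 600 to 700 per group. This is why one time point should be named.

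**3. What T1 adds to the precision of the T2 estimate**

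The article gives neither a dropout rate nor correlations between visits, so both are assumed: everyone is seen at T1, 25% then miss T2, and all pairwise correlations are 0.6. Clustering is ignored.

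- Partial T1–T2 correlation given T0: (0.6 − 0.36) / (1 − 0.36) = 0.375; squared, 0.141.
- Variance relative to complete data, T2 completers only: 1 / 0.75 = 1.333.
- Using T1 as well: 0.141 + 0.859 / 0.75 = 1.286.
- Ratio: 1.286 / 1.333 = 0.965, so variance falls by about 3.5% and the standard error by under 2%.

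The reduction equals the squared partial correlation times the proportion missing T2 (0.141 × 0.25 = 0.035), which gives a range:

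- Correlations 0.4, 10% missing: partial 0.24 / 0.84 = 0.286; 0.082 × 0.10 = 0.8%.
- Correlations 0.8, 40% missing: partial 0.16 / 0.36 = 0.444; 0.198 × 0.40 = 7.9%.

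**4. Dropout**

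Analysing T2 completers with T0 adjustment is sound if missing T2 depends only on group, T0 and the other covariates. If it also depends on the T1 score, that analysis is in general biased. A joint likelihood model for T1 and T2 remains valid if data are missing at random given the observed scores and covariates and the model is correctly specified.

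**The case against.** The strongest reply is that a one-year analysis is plainly intended. The Discussion promises one, the T1 data are collected, and the analysis section opens with mixed models for every outcome; the T2 sentence may only illustrate the model's form. The article is condensed, and an analysis plan that is not shown may contain a T1 model.

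Part of this stands. A reader might infer that the T1 wave is to be discarded or that the end-of-programme effect will never be estimated. The Discussion does not support that: it shows an omission in the model text, not a decision to drop the data. But the article is not merely silent. It specifies response, covariates, random effect and time points, and limits follow-up to T2 in both paragraphs. An analysis plan with a T1 model would have to go beyond that text; one that followed it would miss the objective.

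A reader might also infer that T1 is the best predictor of a missing T2 score, or that the T2 estimate is shown to be wrong. Neither follows. With the equal correlations assumed above, T0 predicts T2 just as well and is already in the model, and bias arises only if dropout depends on T1. Multiple imputation could bring T1 in, but it is only to be considered above 30% missing data, and T1 is not named as an input.

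Finally, a joint model is not the only remedy. A separate T0-adjusted model for T1 would remove the contradiction.

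**Conclusion.** The contradiction holds in limited form. The first two objectives and the Discussion cover one and two years, while both written analyses cover T0 and T2 only. One of the two follow-up waves, in both SCs, therefore has no stated model, and professionals seen at T1 but not at T2 add nothing to the individual-level T2 model.

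The effect on T2 precision is minor: about 3.5% in variance under the assumed 25% loss and correlations of 0.6, and 0.8% to 7.9% over the range shown. The point rests on the unanswered one-year objective and, second, on robustness to dropout related to T1, which requires missing at random and a correct model. The two-year effect does have a written model, and nothing has been lost that the collected data cannot supply. The change does not address the separate matter of having one SC per arm.

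**What to change.** In the Statistical analysis section:

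- **Individual level.** Use T1 and T2 scores as joint responses in a repeated-measures linear mixed model. Fixed effects: SC group, time, group by time, T0 score, T0 by time, and the covariates already listed. Random effects: person, and unit/department. The T0-by-time term lets the baseline slope differ between visits, as it would in separate models. At minimum, add the existing T0-adjusted model with the T1 score as response.
- **Reporting.** Give the group contrast at each time and name one as primary in advance.
- **Department/unit level.** Add the T1 scores as a third time point beside T0 and T2. The individual-level model does not carry over literally, because here T0 is a time point and there is no person effect.

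The cost is a change of wording and slightly more analysis work. No extra visits or data are needed.

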**Fig. 2 Fig2:**
[figure not shown]
Hierarchical structure of the CHU

The recruitment of SCs before randomisation was conducted in collaboration with CHU-level management according to the following eligibility criteria:
At the CHU management level, agreement by the CHU General Director (*Directeur Général*, DG), the human resources director, the president of the medical community and the general nursing coordinator.No major reorganisation or re-affectation planned over the study period.At the SC management level, agreement by the SC top-manager, the senior chief nursing officer, the senior chief medical officer and the chief nursing officer.Both medical and surgical activity in the SC.

A first random selection was performed among the eligible SCs to determine the two SCs to be included in the study. The randomisation is performed by the scientific committee, which is coordinated by the principal investigator. It comprises the researchers associated with the project (co-authors of this paper).

All the departments in the two SCs were assumed to be included, given the agreement obtained by SC senior management on the strength of its hierarchical responsibility. The SC senior chief medical officer is in charge of information to heads of department, and the SC chief nursing officer is responsible for information to front-line managers.

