### Data collection and randomisation

The data collection is conducted by two clinical research nurses, two occupational physicists and two psychologist trainees. They are managed by a clinical study coordinator. Staff members are specially recruited for this data collection. Their sole supervisor is the study’s principal investigator.

The quantitative indicators are collected at the time of the mandatory check-up in the occupational medicine department in compliance with French law. This check-up is yearly and thus fits the planned data collections in the study.

After information to front-line managers, all the professionals working in the departments in the two SCs are called on to attend the medical check-up. This call takes the form of an internal letter signed by the head of the occupational medicine department, inviting the person to contact the secretariat to make an appointment. In case on non-response by the agent, two telephone reminders can be made by the secretariat.

The consultations are planned over a period of 3 months at most. The professionals are first seen by a clinical research nurse who presents the research protocol and proceeds to inclusion in the study on the following criteria:
any professional working in healthcare departments, whatever their profession (chief medical officer, doctor, front-line manager, nurse, nursing assistant, technical staff, secretariat etc)written agreement by the professional to take part in the quantitative research.

In case of refusal to participate, the professional is taken to a waiting room until he/she sees the occupational physician for the regulatory, non-standardised check-up.

Professionals agreeing to participate are asked to wait around 40 min in the waiting room and during this time to complete a questionnaire on a tablet. The questionnaire enables the collection of psychometric indicators. The participant is then called by the doctor for a check-up lasting around 35 min. The doctor follows a standardised layout and codes the clinical indicators retrieved from the interview and the clinical examination on a computer. At the end of the consultation the doctor can address the person to an occupational nurse for any complementary biological tests required.

Following the inclusion campaign and baseline data collection, a second random selection is performed by the scientific committee to determine which of the two SCs is the “intervention SC” and which serves as the control.

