### Sample size

Our estimate is based on the effect observed by Dahinten (2014) on the overall score for structural empowerment. Given the hierarchical structure of the data in the present study, (“professional” level nested in the ‘“functional unit” level, in turn nested in the “department” level) an inflation factor needs to be applied to the standard calculation of sample size [78]. The calculation of the inflation factor is based on the following hypotheses:
an intra-class Correlation Coefficient (ICC) equal to 0.001 (within-SC correlation) We did not find any estimation in the literature of an ICC corresponding to our main judgement criterion and our study population. However ICC values are classically around 0.001 to 0.1 [79]an alpha risk of 5%a statistical power of 80%a difference of 0.12 points between global structural empowerment scores for professionals in the intervention group between T1 and T2 [42]a standard deviation of the global structural empowerment score of 0.56 points [42]

With these hypotheses, the number of professionals to include per group is 519. In all, 1038 professionals should be included. This expected number is close to the overall numbers of professionals in the two SCs. Given the considerable risk of loss to follow-up, the choice was to aim for an exhaustive coverage of the two SC, i.e. 600 to 700 individuals per group. We also rely on the compulsory nature of the check-up to reach this objective.

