## Discussion

Empowerment is a key factor of occupational health and organizational performance in care facilities. Nevertheless empowering workers remains a managerial challenge as well as a scientific one.

Empowering workforces implies to improve both structural and psychological empowerment. This means, on the one hand, that environment must provide workers resources, support, opportunity and information and also, on the other hand, that the workers experience autonomy, competence, impact and meaning. The purpose is to internalize motivation and finally improve commitment, health and performance.

But these processes need a real transformation of managerial practices from the top to first-line management level, for the purpose of sustainably and truly enhancing the powers of workers [18, 82].

Therefore, the main strength of the CHRYSALIDE study consists of the intervention design which combines accompaniment of healthcare teams with training and accompaniment of front-line managers and training and accompaniment of SC-level managers [83].

The results of this study will contribute to address the need for concrete methodology to empower workforces in care facilities, by transforming managerial practices of all the hierarchical strata [82, 84].

With this aim, the series of measurements assesses a wide range of the empowerment predictors and outcomes and also mediators (such as motivational processes), while combining self and hetero-evaluation, enabling strong measures and precise analysis of the effects of the intervention and enriching discussions for the design of future interventional studies [44].

Furthermore, measurements are made during mandatory medical check-ups in the Occupational Medicine Department of the CHU. This recruitment strategy should enhance follow-up at 2 years.

Obviously the implementation and the results of the analysis of the effects of the intervention at one and 2 years will be reported in a series of scientific articles. In addition to the scientific valorisation, the results will also be circulated to the public authorities and the managerial community of health facilities, at least in France. We hope the results will contribute to reflection on prevention and management policies, and to the development of W-QoL. If the intervention is a success, the system will warrant replication in other SCs and in other health facilities.

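### With one sub-centre per arm, the SC effect and the intervention effect are aliased, so the planned 5% test and 95% CI hold for an intervention effect only if residual SC-level variance is zero

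*Protocol article*

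**What the plan says.** All references are to the protocol article.

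- **Unit of randomisation.** Study design: "The randomisation was therefore performed at SC level". The reason given is the reach of the intervention: "It simultaneously targets healthcare teams, department management and SC management".
- **Number of clusters.** Sub-centers recruitment describes a first draw among eligible SCs "to determine the two SCs to be included in the study". Data collection and randomisation then says that, after baseline, "a second random selection is performed by the scientific committee to determine which of the two SCs is the" intervention SC and which is the control. That is one SC per arm.
- **Analysis.** Statistical analysis has the T2 score "explained by the fixed SC effect (intervention versus control) and by the random effect of the department or unit", adjusted for the T0 score, age, gender, profession, working time and team size, with an alpha of 5%.
- **Sample size.** The inflation factor rests on "an intra-class Correlation Coefficient (ICC) equal to 0.001 (within-SC correlation"). The section adds that ICCs usually lie around 0.001 to 0.1, and arrives at 519 professionals per group.
- **Use of the result.** Background presents the study as a test of efficacy meant to inform public policy. The Discussion says: "If the intervention is a success, the system will warrant replication in other SCs and in other health facilities".

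**The concern.** The fixed effect that the model calls SC is also the arm indicator. Any way in which these two SCs would have diverged between T0 and T2 without the intervention (a change in local leadership, staffing or workload, for example) enters the same coefficient as the intervention. The random effect describes how departments or units vary inside an SC, so it says nothing about how whole SCs vary. With one SC per arm there are zero degrees of freedom for that component.

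The two statistical sections also differ on this. The sample size allows for SC-level correlation, while the test and CI are built as if there were none. If any SC-level variance remains after adjustment, the CI is too narrow for an intervention effect and a nominal 5% test rejects too often. What is at stake is whether a significant coefficient may be read as the effect of the programme or only as a difference between two SCs.

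**Working it through.** **1. Reproduce the plan's sample size.** Inputs from Sample size: difference 0.12, SD 0.56, alpha 5% (sidedness is not stated; two-sided reproduces the figure), power 80%, ICC 0.001.

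- Before inflation: n0 = 2 × [0.56 × (1.960 + 0.842) / 0.12]² = 341.9, so 342 per group.
- Design effect 1 + (m − 1) × ICC with the whole arm as one cluster (m = n): n = 342 × 0.999 / (1 − 342 × 0.001) = 341.66 / 0.658 = 519.2. This matches the stated 519; the design effect is 519 / 342 = 1.52.
- Other cluster sizes do not match: m = 20 (about one unit) gives 348, m = 600 gives 547, m = 1000 gives 684.

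The 0.001 is therefore an SC-level ICC, applied with one cluster per arm.

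**2. Variance the model sees and variance the design has.** In units of the outcome variance, with K departments per SC, n staff per SC, department ICC ρd and SC ICC ρs:

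- modelled variance: Vm = 2 × [ρd / K + (1 − ρd − ρs) / n]
- actual variance: Vt = Vm + 2ρs
- actual type I error of a nominal 5% test: 2 × [1 − Φ(1.96 × √(Vm / Vt))]

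From the protocol: K = 5.5 (midpoint of five to six departments), n = 519 up to 700 (top of the coverage target), ρs = 0.001, with 0.01 inside the cited range. **Assumed, not in the protocol:** ρd = 0, 0.02 or 0.05, and a residual SC ICC after adjustment equal to the ρs used.

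Example (ρs = 0.001, ρd = 0, n = 519): Vm = 2 × 0.999 / 519 = 0.00385; Vt = 0.00385 + 0.002 = 0.00585; ratio 1.52; error 2 × [1 − Φ(1.96 / √1.52)] = 11.2%.

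| SC ICC | Department ICC (assumed) | Vt / Vm | Actual type I error |
|---|---|---|---|
| 0.001 | 0 | 1.52-1.70 | 11-13% |
| 0.001 | 0.02 | 1.18-1.20 | about 7% |
| 0.001 | 0.05 | 1.09-1.10 | about 6% |
| 0.01 | 0 | 6.2-8.1 | 43-49% |
| 0.01 | 0.02 | 2.8-3.0 | 24-26% |
| 0.01 | 0.05 | 1.9-2.0 | about 16% |

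Ranges run from n = 519 to n = 700. A t reference with 9 df (11 departments less 2) is slightly lower: for ρd = 0.02, 6.7-6.9% at SC ICC 0.001 and 21-22% at 0.01.

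**3. Interval width.** At n = 519, ρd = 0 and SC ICC 0.001, the 95% half-width is 1.96 × 0.56 × √0.00385 = 0.068 as modelled and 1.96 × 0.56 × √0.00585 = 0.084 with the SC component. The planning difference is 0.12.

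**4. Check by simulation.** With 22 units per arm, 600 staff per arm, an assumed unit ICC of 0.02 and a t-test on unit means, rejection under no effect was 5.1% at SC ICC 0, 9.1% at 0.001 and 36.7% at 0.01. The unit random effect does its job within SCs and leaves the SC component untouched.

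**The case against.** Several points on the other side stand.

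- **Safeguards exist.** The model adjusts for the T0 score. Eligibility required that no large restructuring was foreseen and that each SC had both medical and surgical activity, and both SCs belong to one hospital complex. These reduce SC differences. They do not remove change specific to one SC over two years.
- **The relevant ICC is unknown.** It is the residual SC-level ICC after adjustment, which may be above or below the planning 0.001. A reader might take 11-13% as the trial's real error rate. The protocol does not support that: the figure belongs to the case with no department variance, and the analysis expects such variance. With modest department variance and the planning ICC, the excess is one or two percentage points. The large figures need an SC ICC ten times the planned one, though still within the range the protocol cites.
- **No usable term was left out.** A reader might infer that the model forgot an SC random effect that could be added. It could not be estimated from two SCs, so the flaw lies in the design and in how the result is to be read.
- **Success is not defined as p < 0.05.** A reader might infer that a significant result is to be declared efficacy. The Discussion does not say so, replication elsewhere is a fairly modest conclusion, and Background and Objectives openly state the comparison as one intervention SC against one control SC. Still, the effect is tested at 5% in a study presented as a test of efficacy, and the text shown does not acknowledge the aliasing.

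Leaving the matter to a separate analysis plan does not answer it: the model is stated here, and no later plan can recover between-SC variance from two SCs.

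**Conclusion.** The concern holds as a limit of the design that the analysis section does not carry through. The coefficient estimates the difference between these two SCs. Its model-based 5% test and CI apply to an intervention effect only if residual SC-level variance is exactly zero, which does not fit the non-zero SC-level ICC behind the 519 per group.

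The size is a range. At the protocol's own ICC of 0.001 the type I error is roughly 6% to 13%, depending on department variance. At 0.01 it is roughly 16% to 49%. Both rest on the residual SC ICC equalling the value used and on assumed department ICCs of 0 to 0.05. The direction is certain whenever SC-level variance is above zero; the amount cannot be known from this trial.

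**What to change.** 1. **Statistical analysis, wording.** State that the SC coefficient and its model-based CI describe the difference between these two SCs, conditional on them, and that neither the 5% test nor that CI alone will be taken as evidence of intervention efficacy. Dropping the p-value while keeping the same CI would change nothing, since both use the same standard error.
2. **Sensitivity analysis, pre-specified.** Add 2 × ρ_SC × σ² to the variance of the contrast for ρ_SC from 0.001 to 0.1. Report the widened CIs and the ρ_SC at which the CI first includes 0. Illustration: an observed difference of 0.12 with n = 519, SD 0.56 and no department variance has modelled variance 0.3136 × 0.00385 = 0.00121, and the CI reaches 0 at ρ_SC = [(0.12 / 1.96)² − 0.00121] / (2 × 0.3136) = 0.004.
3. **Conclusion.** Limit it to what that analysis supports.
4. **Optional.** For the institutional indicators only (absenteeism, unit performance, adverse events, schedule compliance), and if they are held across the whole complex, use the other SCs to gauge between-SC variation. This does not cover structural empowerment or the other questionnaire outcomes.

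The cost is some wording and one table, plus a data extract if item 4 is taken up. The downside is a less favourable headline claim.

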### Sub-centers recruitment

The targeted CHU comprises 12 SCs with five to six departments each, each in turn grouping a number of care units for a total of 20 to 25 per SC. The size of the SCs varies from 800 to more than 1000 salaried staff. The hierarchical structure is presented in Fig. 2.

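### The outcome model names one random effect, for department or unit, although units are nested in departments; the unit-only model this permits understates the standard error of the SC contrast

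*Protocol article*

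**What the plan says.** All references are to the Protocol article.

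- **Hierarchy.** The Sample size section places professionals in functional units, which are "in turn nested in the “department” level". Sub-centers recruitment gives the number of departments: "The targeted CHU comprises 12 SCs with five to six departments each". The same section puts the number of care units in an SC at between 20 and 25.
- **Allocation.** Under Study design: "The randomisation was therefore performed at SC level". One SC receives the intervention and one is the control.
- **Model.** The Statistical analysis section introduces mixed linear models "while taking into account the hierarchical nature of the data". It then names a fixed SC effect, baseline covariates, and one random term: the T2 score is explained in part "by the random effect of the department or unit".
- **ICC.** The same alternative returns: "The ICC will be estimated to have a precise idea of the effect of the department or unit".

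No sentence says that both levels enter together as nested effects, and none says which level is used if only one does.

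**The concern.** The article declares three levels and then writes a model whose random part has one term, at either of two levels. The choice affects the SC contrast. If departments differ from one another, units within a department are correlated. A unit-only model spreads the department variance over 20–25 supposedly independent units per SC, when it really averages over only five or six departments.

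Department-level variation is plausible on the article's own account. Each department has its own facilitator and diagnostic report, a department head's objection can stop the intervention there, and the analysis text itself expects implementation to vary between departments and units.

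At stake are the confidence interval and p-value for the SC effect on every outcome analysed at the individual level. If the level is picked after the data are seen, the version with more clusters will tend to look more precise than it is.

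**Working it through.** **1. The article's own figure.** With a difference of 0.12, SD 0.56, two-sided 5% and 80% power, the unadjusted size is 2 × (1.960 + 0.842)² × 0.56² / 0.12² = 341.9, so 342 per group. Using ICC 0.001 with the whole arm as one cluster, n = 342 × (1 − 0.001) / (1 − 342 × 0.001) = 519, as stated. With clusters of 20 to 100 people the result would be only about 348 to 376. The planning ICC of 0.001 is therefore a within-SC value, as the article labels it. It is not a department or unit ICC, and the documents give neither.

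**2. Inputs for the check.**
- From the article: D = 5–6 departments and U = 20–25 units per SC; N = 600 per SC (lower end of its 600–700 target); ICC range 0.001–0.1.
- Assumed: department ICC ρd from 0.001 to 0.1, unit ICC ρu from 0 to 0.05, near-balanced sizes, no SC-level variance.

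**3. Formulas** (variances in units of the total SD²).
- Actual variance of the SC difference: V = 2[ρd/D + ρu/U + (1 − ρd − ρu)/N].
- Between-unit variance that a unit-only model sees within an SC: b = ρu + ρd(U − U/D)/(U − 1).
- Variance that the unit-only model reports: V* = 2[b/U + (1 − ρd − ρu)/N].
- False-positive rate at nominal 5%: 2[1 − Φ(1.96/√(V/V*))].

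**4. One case in full:** ρd = 0.01, ρu = 0, D = 5, U = 25.
- V = 2(0.01/5 + 0.99/600) = 0.00730.
- b = 0.01 × 20/24 = 0.00833, so V* = 2(0.00833/25 + 0.99/600) = 0.00397.
- V/V* = 1.84. In score points the standard error is 0.56√0.00730 = 0.048, but the model reports 0.56√0.00397 = 0.035. The false-positive rate is 14.9%.

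**5. Ends of the range.**

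| Department ICC | Mildest case (D=6, U=20, ρu=0.05): V/V*, rate | Worst case (D=5, U=25, ρu=0): V/V*, rate |
|---|---|---|
| 0.001 | 1.03, 5.3% | 1.10, 6.1% |
| 0.01 | 1.27, 8.2% | 1.84, 14.9% |
| 0.05 | 1.99, 16.5% | 3.56, 29.9% |
| 0.1 | 2.48, 21.3% | 4.45, 35.3% |

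At ρd = 0 the ratio is 1 and nothing is lost. Replacing 1.96 by the t value on unit-level degrees of freedom (2U − 2 = 38 to 48, about 2.02 to 2.01) lowers the rates only a little: 4.6–5.5%, 7.3–13.8%, 15.1–28.7% and 19.9–34.0%.

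**6. Simulation** (balanced data, 600 per arm, 6,000 replicates per scenario). Unit-only tests rejected in about 4–5% of replicates at department ICC 0.001, 10–13% at 0.01, 18–25% at 0.05 and 30–35% at 0.1. A t-test on department means (8–10 df) stayed at 4.5–5.7% throughout.

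**The case against.** - **The word 'or' may be loose.** The sentence before it speaks of variation across departments or units in a way that covers both, the stated aim is to respect the hierarchy, and an article condenses a fuller plan. This stands in part: a reader might infer that the plan commits to a unit-only model, and it does not. But the article does write out the model, with its fixed effect, random term and covariates, and that random term does not carry the hierarchy the article declares. The text permits the harmful version.
- **The size depends on an unknown ICC.** This stands. At a department ICC of 0.001 the effect is negligible. Adjustment for the T0 score, profession and team size may also bring the residual ICC below the raw one.
- **Unit is a real delivery level too.** Feedback and negotiation meetings take place in each unit. This stands, and it argues for keeping both levels.
- **Department-only is said to be too liberal as well.** A reader might infer this from the 10–12 clusters. The article names no critical value or degrees of freedom, so it cannot be charged with using 1.96, and the department-level check above held its nominal level. Likewise, the article's hope for a precise idea of the ICC is a matter of wording and not an error in the analysis.

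**Conclusion.** The point holds in a limited form. The model as written leaves the random level open, and one of the options it permits, unit only, understates the standard error of the SC contrast whenever between-department variance is above zero. Under the stated assumptions the false-positive rate runs from about 5–6% at a department ICC of 0.001, through 8–15% at 0.01 and 16–30% at 0.05, to 21–35% at 0.1. These figures are conditional on assumed ICCs; they do not predict this trial's error rate.

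A reader might also infer that naming both levels would make the inference valid. The documents do not support that. With one SC per arm, any difference between the two SCs is confounded with the intervention, SC-level variance cannot be estimated, and every standard error discussed here omits it. The present point is secondary to that limit, but it can be repaired in the plan.

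**What to change.** In the Statistical analysis section, replace "by the random effect of the department or unit" with random intercepts for department and for unit within department, both always retained whatever their estimated size. Test the SC coefficient against degrees of freedom that reflect the 10–12 departments, for example Kenward-Roger or Satterthwaite. State beside it that SC-level variance is not estimable with one SC per arm and is not included in the reported standard errors.

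The cost is a sentence or two in the plan and somewhat wider confidence intervals. No additional data are needed, since the design already identifies department and unit.
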